### Study design

All health facilities providing EPI services in selected study sites and corresponding catchment populations will be eligible for inclusion and constitute the primary sampling unit for this evaluation. Health facilities will be randomly selected for inclusion (Fig. 3). All non-EPI/PMC facilities within the selected EPI catchment areas, will be included in the passive cohort data collection, described below (Table 1). In the selected EPI facility catchment areas, several study activities will be conducted: (i) a census to enumerate all households, primary caregivers and children under 36 to characterize the population eligible to receive PMC (0–24 months) as well as when they age out of the intervention (25–36 months), (ii) a passive cohort at health facilities to monitor clinical episodes of malaria and anaemia as well as receipt of EPI vaccinations and PMC in children under 36 months, and (iii) to monitor malaria and anaemia in a subgroup of participating children in an active cohort over an 18-month period. The same procedures will be employed in both intervention and control areas in Cameroon and Côte d’Ivoire.

**Table 1 Tab1:** Eligibility criteria for each study component in the PMC impact evaluation study

	Inclusion Criteria	Exclusion Criteria
**Health Facilities**	- Located within the target study sites - Administer EPI/PMC services	- Located outside of the target study area
**Census - Household**	- Located within the catchment area of selected health facilities - Head of household provides consent	- Located outside of the selected health facility catchment area - Head of household not present or refuses participation
**Passive Cohort - Child**	- Regularly resides in households included in the census - Age 36 months or less at time of census - Primary caregiver provides informed consent	- Head of household refused participation in the census - Primary caregiver not present or refuses participation - Not expected to reside in the selected household for the study duration - Age greater than 36 months of age at recruitment visit

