**Active Cohort - Child**	- Recruited into the passive cohort - Aged between 6–9 months in Cameroon and 10 weeks and 6 months in Côte d’Ivoire at point of recruitment - Primary caregiver provides informed consent	- Head of household/caregiver refused participation in the census and/or passive cohort - Not within the identified age category at the point of recruitment - Primary caregiver not present or refuses participation

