### Active cohort

The active cohort will measure malaria infection, anaemia, and malnutrition incidence in the intervention and control study populations in Cameroon and Côte d’Ivoire. The sampling frame for the active cohort will consist of the children whose primary caregiver provided consent for participation in the passive cohort (Table 1). Children between 6 and 9 months and 10 weeks and 6 months of age at recruitment in Cameroon and Côte d’Ivoire, respectively, will be approached for inclusion. Targeting these age ranges will maximize study power to measure differences between the PMC intervention and standard of care in each country within the 18-month study period. The target age range was also defined to ensure at least one sampling time point after the final potential PMC dose to observe any change in risk of malaria infection after aging out of the intervention [13]. Recruitment into the active cohort will continue until the target sample size is achieved.

At the initial household visit for children enrolled in the active cohort, field workers will record the household and child ID number assigned during the census and collect detailed information related to malaria risk factors including household construction and use of vector control interventions. A detailed questionnaire on recent fevers, malaria history, care seeking behaviours, EPI vaccines received to date, and other relevant factors will also be collected. Children will be assessed for fever, anaemia, malaria, and malnutrition. First, forehead temperature will be taken using an infrared thermometer with fever defined as those with temperature > 37.5 °C. A capillary blood sample by heel or fingerpick will be collected using a sterile lancet and aseptic technique on all children. The blood sample will be used to measure: (i) haemoglobin (Hb) levels with a photometer (HemoCue^®^ Hb 301, Angleholm, Sweden), devices, (ii) conduct a malaria rapid diagnostic test (RDT), (iii) prepare a thin and thick blood slide for malaria microscopy and (iv) to collect blood spots on filter paper. The mid-upper-arm circumference will be collected from all enrolled children to screen for malnutrition and monitor growth trajectories over time. Treatment for malaria, anaemia and malnutrition will be offered according to national guidelines. Any children with a fever or who are severely ill will be referred to the nearest health facility for treatment.

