Each child in the active cohort will be followed-up for a maximum of seven visits at three-monthly intervals over 18 months, including the initial recruitment visit plus six subsequent follow-up visits (Fig. 4). During follow up visits at the household, verbal consent from the primary caregiver for continued participation of their child in the study will be recorded. A short questionnaire will be completed to collect data about any malaria or anaemia diagnosis or receipt of PMC since the last study visit, at which health facility care was sought and other relevant information. A blood sample will be collected following the same procedures outlined above.

Adverse events and safety of receiving PMC will be monitored by the MoH as part of the routine programmatic implementation of this intervention. Participant safety will be monitored throughout the study period and any adverse effects related to study procedures will be investigated using standardised procedures and managed according to national guidelines.

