### Data analysis

The primary analysis will be based on intention to treat (ITT), including all children residing in the intervention area as the exposed group. All available data up to the time of censuring (e.g., loss to follow-up, withdrawal, death, or study completion), irrespective of whether the child received any, part, or all the intended PMC doses. An additional per-protocol analysis will be completed which includes children who received at least one dose, all doses, or specific doses of PMC. The period of protection provided by SP is up to one-month post treatment and thus will constitute the protective window of those receiving the intervention. Data for both countries will be combined for analysis as well as assessed separately to ensure context specific nuances are fully assessed.

Incidence rates for malaria and anaemia will be calculated using multivariable Poisson regression, difference-in-difference, and interrupted time-series models comparing intervention and control areas [14–16]. Incidence rates, rate differences, and rate ratios between intervention and control area will be calculated for the ITT and per-protocol analysis. Malaria incidence will be determined by the number of malaria cases confirmed by either RDT or microscopy identified in either the passive or active cohort. Person-time at risk for each study outcome will be calculated based on the date of recruitment into the study population until the date of censuring or study end. For children who leave the study prior to the end date, the date of exit will be the date where they moved, withdrew from the study, or died. If that date is not known, the midpoint between the date of last contact and the date the loss was detected will be used. Protective effectiveness will be calculated for the intervention period including the 18 months of follow-up for the periods where PMC doses differ, stratified by first and second year of life, as well as during the post-intervention period, starting at 24 or 18 months of age in Cameroon and Côte d’Ivoire, respectively, to estimate any potential rebound in malaria.

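### The malaria incidence rate mixes care-sought cases with infections found by screening a nested subgroup, and lets positives at recruitment count as events

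*Protocol article*

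**What the plan says.** The protocol article gives one definition of the malaria numerator. Under Data analysis it is the "number of malaria cases confirmed by either RDT or microscopy identified in either the passive or active cohort". The denominator follows in the same section: "Person-time at risk for each study outcome will be calculated based on the date of recruitment into the study population", running to censoring or study end.

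The two cohorts are nested. Table 1 under Study design requires an active-cohort child to be "Recruited into the passive cohort", and the purpose of the active cohort is "to monitor malaria and anaemia in a subgroup of participating children in an active cohort over an 18-month period".

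The two cohorts detect different things. The passive cohort records visits that enrolled children make to study facilities or CHWs. For the active cohort the plan says: "The active cohort will measure malaria infection, anaemia, and malnutrition incidence in the intervention and control study populations". Testing there does not depend on symptoms: "A capillary blood sample by heel or fingerpick will be collected using a sterile lancet and aseptic technique on all children", and the sample is used for both an RDT and a blood slide. Each child has a "maximum of seven visits at three-monthly intervals over 18 months, including the initial recruitment visit plus six subsequent follow-up visits".

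The cohorts also feed each other: "Any children with a fever or who are severely ill will be referred to the nearest health facility for treatment". The Passive cohort section then has staff record the date, diagnosis and treatment when an enrolled child visits a study facility.

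For repeated records in one child, Data analysis provides random effects or GEE. The Discussion says that unique child IDs link records across both cohorts.

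**The concern.** Followed as written, the rule puts two kinds of event into one rate: illness for which care was sought, and infection found by testing every child on a schedule. Only the nested subgroup can contribute the second kind, so the rate depends on how many children are in that subgroup as well as on malaria.

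Three consequences follow.

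- **Mixed meaning.** The rate is neither clinical malaria nor infection. The Background section itself cites clinical malaria and parasitaemia as separate outcomes with separate rate ratios.
- **Recruitment positives.** A positive at the recruitment visit falls on the day person-time starts, so it would be an event with no time at risk. It also reflects exposure before follow-up began.
- **Possible double records.** A febrile child who tests positive at home is referred to a facility, where the same illness can be recorded again. Random effects and GEE model within-child correlation; they do not remove duplicates.

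There is also a comparability problem inside the study. Children aged 24 to 36 months at baseline are meant to serve as an internal control, but they are outside the active-cohort recruitment ages. A combined count would ascertain them differently from the younger children who are screened.

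**Working it through.** **Inputs from the protocol article.** Background rates are 0.597 per child-year in Cameroon and 0.572 in Côte d'Ivoire (under-5 incidence in 2020, Study site). Planned reductions are 30% and 40% (Sample size), so the planned ratios are 0.70 and 0.60. Follow-up is 1.5 years with seven tests, the first at recruitment.

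**Assumptions.** The under-5 rates stand in for the care-sought rate in control children. Positivity *p* at each visit is not in the document and is ranged from 5% to 30%. Every positive is counted, and there is no loss to follow-up.

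**1. Starting point without screening, Cameroon.** Control: 0.597 × 1.5 = 0.896 cases per child. Intervention: 0.896 × 0.70 = 0.627. The ratio is the planned 0.70.

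**2. How much of the count is screening.** Six follow-up tests in 1.5 years add 6*p*/1.5 = 4*p* positives per child-year. Their share of the active-cohort count is 4*p*/(4*p* + 0.597):
- *p* = 5%: 0.2/0.797 = 25%
- *p* = 15%: 0.6/1.197 = 50%
- *p* = 30%: 1.2/1.797 = 67%

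**3. Effect on the ratio in active-cohort children.** Control count = 0.896 + 7*p*. The intervention count depends on what PMC does to positivity (Cameroon):
- Only the recruitment visit unaffected: 0.627 + *p* + 6*p* × 0.70
- Half the effect at all visits: 0.627 + 7*p* × 0.85
- No effect: 0.627 + 7*p*

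At *p* = 5% the control count is 1.246, a rate of 0.83 per child-year. The ratios are 0.887/1.246 = 0.71, 0.924/1.246 = 0.74 and 0.977/1.246 = 0.78. At *p* = 30% the control count is 2.996, a rate of 2.00. The ratios are 2.187/2.996 = 0.73, 2.412/2.996 = 0.81 and 2.727/2.996 = 0.91.

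| PMC effect on positivity | Cameroon (planned 0.70) | Côte d'Ivoire (planned 0.60) |
|---|---|---|
| Absent at recruitment visit only | 0.71–0.73 | 0.62–0.64 |
| Half | 0.74–0.81 | 0.66–0.74 |
| None | 0.78–0.91 | 0.72–0.88 |

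Dropping recruitment positives (six visits) restores 0.70 only in the first case. For Cameroon the other two become 0.74–0.80 and 0.78–0.90, so that step alone is not enough.

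**4. Unequal screening shares.** Take all passive-cohort children in Cameroon, with *p* = 10%, six follow-up tests and the full 30% effect on positivity. If 30% of intervention and 10% of control children are screened, the ratio is (0.627 + 0.3 × 0.6 × 0.70)/(0.896 + 0.1 × 0.6) = 0.753/0.956 = 0.79. With the shares reversed it is 0.669/1.076 = 0.62. With equal shares it stays at 0.70.

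**5. Double records.** If 10% of cases are duplicated in both areas, the Cameroon control rate rises from 0.597 to 0.657 and the ratio stays at 0.70. If 5–20% are duplicated in one area only, the ratio is 0.67–0.58 (control only) or 0.74–0.84 (intervention only).

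**The case against.** The strongest reply is that this reads a counting algorithm into one condensed sentence. Naming both cohorts as sources does not say that two records of one infection are added. Separate analyses by cohort are not ruled out, and linked IDs make merging possible. Episode windows, merging rules and removal of person-time after treatment are ordinary SAP content, so their absence from an article is no error. All of that stands. What it does not answer is that the article does state a numerator and a start of person-time, and together these combine two kinds of event and admit recruitment positives. An episode window elsewhere would not separate clinical cases from screened infections.

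A reader might also infer stronger claims that the documents do not support:

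- **That double counting by itself biases the effect.** Step 5 shows that equal duplication leaves the ratio unchanged. Differential duplication is possible but not shown.
- **That screening shares do differ between areas.** Planned numbers per facility are equal: 1,560/26 = 540/9 = 60 in Cameroon and 1,148/14 = 410/5 = 82 in Côte d'Ivoire. Shares would differ through catchment size, which is not given.
- **That every screened positive is prevalent infection miscounted as incident.** Malaria treatment is offered at household visits, so a positive in a child who was negative or treated three months before can be a true incident infection with an unknown date. Only the recruitment visit clearly fits the charge.
- **That a quarterly positive can reflect PMC only within about a month of a dose.** Infections may persist, and PMC is a full treatment course given whether or not the child is infected, so an effect on later tests is plausible.
- **That a large share of all facility cases would be recounted at the next visit.** Only active-cohort children have a next visit, and the document gives no duration of RDT positivity.

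The plan also has a reason to use active detection: Aims and objectives notes that passive data miss children who do not seek care.

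**Conclusion.** The concern holds as a badly fixed outcome definition. It does not establish that infections will be counted twice or that the ratio will be biased. As written, the malaria rate mixes care-sought cases with screened infections in proportions set by sampling, and a recruitment positive enters with no time at risk.

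The size cannot be fixed from the document. The distortion in Cameroon runs from negligible (0.71 against 0.70) to most of the planned effect (0.91). Where it falls depends mainly on how far PMC lowers infection prevalence, and then on positivity. Both are assumptions here. These ratios apply to active-cohort children; in the whole passive cohort, dilution is weaker because only some children are screened, but differing shares could then move the ratio either way.

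**What to change.** State two malaria outcomes in place of one:

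1. **Clinical malaria:** test-confirmed cases detected at facilities and by CHWs, ascertained alike in all passive-cohort children of both areas.
2. **Infection (and anaemia) in the active cohort:** follow-up visits only, analysed as visit-level prevalence or as interval-censored incidence.

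Use recruitment-visit results as baseline covariates, not as events. Use the linked child IDs to count one infection once, with a prespecified episode window and matching removal of person-time. Say which of the two outcomes is primary. A combined active-cohort rate can stay as a secondary analysis.

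The cost is in outcome definition and analysis text; no new data are needed. The clinical rate will have fewer events and will again depend on care seeking, which the separate infection outcome offsets.

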**Methods:**

We will assess the impact of PMC using passive and active monitoring of a prospective observational cohort of children up to 36 months of age at recruitment in selected study sites in Cameroon and Côte d’Ivoire. The primary and secondary outcomes include malaria, anaemia and malnutrition incidence. We will also conduct a time-series analysis of passively detected malaria and anaemia cases comparing the periods before and after PMC introduction. This study is powered to detect a 30% and 40% reduction of malaria incidence compared to the standard of care in Cameroon and Côte d’Ivoire, respectively.

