### Census

A census of the population will be conducted in each selected EPI catchment area to create a sampling frame that will support both the passive and active cohorts. Specifically, all households in the selected EPI catchment areas will be approached for inclusion (Table 1). Written, informed consent will be obtained from the head of household for participation in the study. Information recorded will include the GPS coordinates of the household, information on house construction, socioeconomic position, use of vector control interventions, healthcare-seeking behaviours, and the number of people residing in the household composition according to age groups. (i) ≤ 3 years, (ii) > 3 to < 5 years, (iii) ≥ 5 years to < 21 years, and (iv) ≥ to 21 years. Each household will be assigned a unique, non-identifiable number that will be included on study documentation and written on household’s doorframe for future localisation.

The census will take place prior to the PMC implementation and will be updated at 3-monthly intervals throughout the 18-month study period. During the census update, any births, deaths, or immigration and emigration will be recorded. The same study procedures during the initial census visit will be followed for new recruits. For any participants that have died since the previous visit, a brief questionnaire will be administered where possible to obtain information on the date of death, whether it was in a health facility or at home, and broad categories of the potential cause of death (i.e., traffic accident, health episode etc.) and other relevant information. Due to the sensitive nature of this data and difficulty in obtaining the precise cause of death in the community, verbal autopsies will not be conducted and any deaths without a confirmed cause of death will be excluded from analysis.

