### Passive cohort

All children up to 36 months of age residing in enumerated households during the census will be eligible for inclusion in the passive cohort and enrolled upon provision of written informed consent from their primary caregiver (Table 1). Enrolled children will be passively monitored to record both EPI vaccinations and PMC visits as well as clinical visits for malaria and anaemia to the health facility and/or CHWs over the 18-month study period. Older children (24 to 36 months at baseline) are not eligible to receive the intervention but will be enrolled in this study activity for two reasons: first, the older children will serve as an internal control as it is assumed that they will experience a similar malaria transmission intensity but will not receive the intervention and, secondly, as children will be followed for 18 months information will be available on children who age-out of eligibility to assess any impact beyond when children are eligible to receive PMC. Children will not be censored according to age.

During the passive cohort recruitment, trained fieldworkers will record basic demographic information about the child, recent malaria cases, amongst other information. An anonymous and unique QR code with the participant ID linked will be attached to each child’s health and vaccination record books. This QR code will be used to identify children participating in the study when they interact with the health system and facilitate linking the data generated by the routine system on EPI, PMC or clinical visit, which are stored in separate registers, with the research activities. During recruitment, the national health ID number assigned to each child and written in the health and/or vaccination record books will be recorded. The names of children and primary caregivers will also be recorded to provide a means to verify that children present match ID numbers. This also serves as a back-up method to link health information data that is routinely collected in different registers. Caregivers will be encouraged to take children to the participating facilities or CHWs to receive EPI vaccinations or PMC or for any illnesses.

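### ITT person-time starts at recruitment, which for first-census children precedes PMC, and the separate protective-effectiveness window does not settle whether that time counts as exposed

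*Protocol article*

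**What the plan says.** On sequence, the Census section of the protocol article states: "The census will take place prior to the PMC implementation and will be updated at 3-monthly intervals throughout the 18-month study period". The Passive cohort section adds: "All children up to 36 months of age residing in enumerated households during the census will be eligible for inclusion in the passive cohort". Consenting procedures places both the head-of-household and the caregiver consent at the census.

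On the ITT analysis, the Data analysis section defines the comparison as "including all children residing in the intervention area as the exposed group" and uses all data up to censoring, whatever doses the child received. The clock is set by this sentence: "Person-time at risk for each study outcome will be calculated based on the date of recruitment into the study population". Incidence rates, rate differences and rate ratios are then to be calculated for the ITT analysis. Malaria cases from either cohort count.

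On effectiveness, the same section states: "Protective effectiveness will be calculated for the intervention period including the 18 months of follow-up for the periods where PMC doses differ". That estimate is stratified by year of life, and a further estimate is planned "as well as during the post-intervention period, starting at 24 or 18 months of age", depending on the country.

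On models, the section lists "multivariable Poisson regression, difference-in-difference, and interrupted time-series models comparing intervention and control areas". The abstract also announces a time-series analysis of passively detected cases "comparing the periods before and after PMC introduction".

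**The concern.** ITT properly ignores whether a child took the doses on offer. It gives no reason to count time before the programme offered them. A child enrolled at the first census in Soa or Séguéla is recruited before PMC implementation there, yet the person-time rule starts that child's clock at recruitment and the exposure rule depends only on residence. Neither refers to a PMC start date.

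In that early time the project's doses do not yet separate the two areas. In Cameroon this means that the expanded schedule has not yet been added to the five-dose standard of care. Any contrast in that period is background. Pooling it with post-introduction time moves the rate ratio toward 1 and understates the programme's effect in the ITT estimate. In a non-randomised comparison with one intervention area and one control area per country, it also mixes into the effect estimate the child-level time that could show how the two areas compared beforehand.

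**Working it through.** **Step 1: sequence against rule.** The first census precedes PMC; passive-cohort children are enrolled and consented at it; person-time starts at recruitment; residence defines exposure. Followed literally, these four statements make first-census children's pre-PMC time exposed time. The effectiveness sentence suggests a narrower window, but its stated bounds are ages and it gives no calendar start. It also folds in the whole 18 months of follow-up and is not linked to the ITT rate ratios.

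**Step 2: size of the dilution.**

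Inputs: 18 months of follow-up; planned reductions of 30% (RR 0.70, Cameroon) and 40% (RR 0.60, Côte d'Ivoire), from Sample size. A pre-PMC rate ratio of 1 is consistent with the Study site figures, which give both areas of a country the same 2020 incidence (597 and 572 per 1,000 children under 5). The gap g between recruitment and PMC start is not in the text; 1, 3 and 6 months are assumptions. The rate is taken as constant, and every child is given the full gap.

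Formula: observed RR = g/18 + (1 − g/18) × true RR.

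| Gap (months) | True RR 0.70 | True RR 0.60 |
|---|---|---|
| 0 | 0.700 | 0.600 |
| 1 | 0.056 + 0.944 × 0.70 = 0.717 | 0.056 + 0.944 × 0.60 = 0.622 |
| 3 | 0.167 + 0.833 × 0.70 = 0.750 | 0.167 + 0.833 × 0.60 = 0.667 |
| 6 | 0.333 + 0.667 × 0.70 = 0.800 | 0.333 + 0.667 × 0.60 = 0.733 |

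Giving every child the full gap makes these upper bounds under the constant-rate assumption, because children added at census updates after PMC starts may bring no pre-PMC time. A gap falling in a rainy season would weigh more than its length suggests.

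**Step 3: illustration in terms of power.** The plan states power only for the active cohort, whose recruitment date relative to PMC start is not given. This step therefore shows what would follow if that cohort had the gap.

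Reproduction of the stated design: Hayes–Bennett formula for two rates, two-sided 5%, 3:1 clusters, with 0.25 used as the between-cluster coefficient of variation k. Sample size calls 0.25 an intra-cluster correlation coefficient, but the stated facility numbers reproduce only if it is read as k. The under-5 incidence figures are assumed to be the planning rates λ0.

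- Person-years per facility, y: Cameroon 1,560/26 = 60 children, × 0.8 × 1.5 = 72; Côte d'Ivoire 1,148/14 = 82, × 0.8 × 1.5 = 98.4.
- Control clusters = 7.85 × [(λ0/y + k²λ0²) + (λ1/y + k²λ1²)/3] / (λ0 − λ1)².
- Cameroon: λ0 0.597, λ1 0.418, giving 8.84 control and 26.5 intervention clusters (stated 9 and 26), power 80.5%.
- Côte d'Ivoire: λ0 0.572, λ1 0.343, giving 4.48 and 13.4 (stated 5 and 14), power 83.8%.

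With a 3-month gap counted as exposed, power falls to about 64% and 68%. If at-risk time starts at PMC introduction instead, the target rate ratio is unchanged, follow-up is 15 months, and power is about 78% and 82%.

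**The case against.** The strongest reply is that the person-time sentence only fixes when a child enters and leaves observation, while the effect is estimated over the narrower window of the protective-effectiveness sentence. Before PMC starts the areas' doses do not differ through the project, so that sentence, on its plain meaning, excludes the early time. This has force, and it means that a diluted headline estimate is not demonstrated. It does not close the matter: the window's stated limits are ages, no PMC start date is named, and the ITT rates and rate ratios are listed separately without reference to it.

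A reader might also infer that the plan throws away all pre-intervention information. The documents do not support that. Difference-in-difference and interrupted time-series models are listed, both need a pre-period, and monthly facility data for up to five years beforehand will be collected by 12-month age band. Those facility data are aggregates, however, and the text does not mark early cohort time as the baseline for any model.

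A third reply is that the size is unknown. That stands. The timeline figure is not available here, and the gap could be days or weeks. The 30% and 40% reductions are active-cohort planning values, and that cohort may lose little or no time.

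Finally, a condensed article may leave the calendar origin to a fuller document. But this article does state an origin, and that origin does not fit its own sequence of census and implementation.

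**Conclusion.** The point holds as an unreconciled definition with a known direction of bias. For the ITT rates and rate ratios, the written rule counts pre-PMC time of first-census children in the intervention area as exposed. If it is applied that way, the rate ratio moves toward 1. The case is clearest for the passive cohort, which also feeds the malaria outcome; for the active cohort it depends on recruitment timing that the text does not give.

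The amount cannot be fixed from the documents. The Step 2 figures rest on an assumed gap shared by every child, a constant rate, equal background incidence in the two areas and a full 18 months of follow-up. With no gap there is no bias. The power figures further assume that the active cohort carries the gap and that 0.25 is a coefficient of variation.

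**What to change.** In the Data analysis section, state that at-risk time for the ITT effect estimates starts, in both areas of each country, at the later of the child's recruitment and one common calendar date: the date PMC was introduced in that country's intervention area. The date should be common to both areas. Facility-specific dates in the intervention area set against an area-wide date in the control area would compare different calendar periods, and transmission is seasonal at these sites.

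Use earlier cohort time only as the pre-intervention baseline, including in the difference-in-difference model already listed. Say whether the protective-effectiveness window starts on the same date, and state the interval between first census and PMC introduction.

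Cost: one or two sentences and one date per country. Person-time falls by the length of the gap for children enrolled before PMC began, which is small for a short gap but one third of 18 months for a 6-month gap. In the 3-month illustration this loss takes power from 80.5% to about 78% in Cameroon and from 83.8% to about 82% in Côte d'Ivoire.
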